### Treatment arms, dosage and route of administration

The intervention is *L reuteri DSM 17938* (0.2x10^8^ cfu per drop as five drops per day) in an oil suspension. Under refrigeration, it is stable for 21 months at 2°C to 8°C (as documented by the manufacturer, BioGaia AB, Stockholm, Sweden). The placebo is maltodextrose in the same oil suspension, identically packaged and stored, and has the same appearance, colour and taste as the intervention. Both intervention and placebo are labeled with only the randomisation number, batch number, expiry date, and the statement “For clinical trial use only”.

Carers administer five drops of study product orally to each infant once daily for 28 days. The dose does not need to be given at a fixed time each day, nor does it need to be given with feeds. However, for compliance and ease of administration, we recommend that families give the dose with the same feed each day.

### Outcome measures

Table 1 shows the primary and secondary outcome measures at different time points of the study. Table 2 shows other information collected at different time points, including family demographics, potential confounders, physical assessments, and records of compliance and side effects.

**Table 1 T1:** Outcome measures

**Construct**	**Timing (D = days/M = months)**						**Measure**	**Additional Information**
	**0**	**D7**	**D14**	**D21**	**D28**	**M6**		
**Primary Outcome**								
Infant crying/fussing time (mins/day)					■		Study diary	A validated measure of infant crying/fussing/sleep/feeding and records these behaviours in 5 minute epochs over 24 hours [65-67]. At baseline parents record in the study diary for 24 hours. At other time-points, the diary is filled in over 48 hours. This is to account for daily variability in infant behaviour whilst taking into account the potential burden to families from filling in the diary for prolonged periods of time.
**Secondary Outcomes**								
Infant crying/fussing time (mins/day)	■	■	■	■		■	Study diary	
Number of episodes of crying/fussing/day	■	■	■	■	■	■	Study diary	
Infant sleep duration (mins/day)	■	■	■	■	■	■	Study diary	
Maternal mental health scores	■				■	■	Edinburgh Postnatal Depression Subscale (EPDS)	A 10-item validated questionnaire to screen for depression in the post-partum setting, with higher scores indicating poorer mental health [68]. Scores of ≥10 and ≥12 are validated to detect postnatal depression in community and clinical settings, respectively.
Parent functioning scores	■				■	■	PedsQL Family Impact Subscale	A 5-item validated questionnaire to assess family functioning, with higher scores indicating better family functioning [69].
Infant functioning scores						■	PedsQL Infant Subscale	A 36-item validated questionnaire used to measure infant physical, emotional, social and cognitive functioning [70].
Parent quality adjusted life years scores	■				■	■	AQol-4R	A 12-item validated questionnaire to assess the health economic parent quality of life [71].
Health service use	■				■	■		Additional health professional visits in relation to infant’s crying.
Infant faecal microbiota diversity	■				■		16SrDNA amplification (T-RFLP)	A molecular method to investigate the diversity within bacterial communities, given as a diversity score, with higher scores indicating more microbial diversity [72].
Infant faecal calprotectin (mg/kg)	■				■		ELISA	An enzyme-linked immunosorbent assay to detect the presence of calprotectin, a marker of gut inflammation [73].
Infant faecal *E coli* load (cfu/ml)	■				■		Quantitative PCR	A molecular method to detect and measure the presence of particular marker genes of *E coli*[74].

**Table 2 T2:** Additional information collected

**Measure**	**Timing (D = days/M = months)**						**Information**	**Details**
	**0**	**D7**	**D14**	**D21**	**D28**	**M6**		
Questionnaire	■						Demographics	
Questionnaire	■						Potential confounders	Family history of atopy. Antenatal / current probiotic / antibiotic use. Smoking during pregnancy. Mode of delivery (caesarean versus vaginal).
Diary questions	■	■	■	■	■	■	Potential confounders	Infant feeding method (breast versus formula). Mother’s intake of dairy, probiotics, medications. Infant’s intake of dairy, probiotics, solids, medications. Infant gastro-oesophageal reflux symptoms (measured by the Infant Gastroesophageal Reflux Questionnaire Revised I-GERQ-R [75,76], a validated measure of infant gastro-oesophageal reflux). Settling techniques. Concurrent illnesses / immunisations.
Diary questions	■	■	■	■	■		Compliance	Number of days study drops missed over preceding week.
Diary questions	■	■	■	■	■		Side effects	Infant stool frequency, consistency.
Physical examination	■						To exclude organic causes of crying	Infants recruited through Maternal Child Health Nurses and Tweddle are examined by the study paediatrician.
Weight	■				■		Weight (kg, to nearest gram)	Measured by the Wedderburn Infant Scale (Tanita Baby Scale Model BD590) calibrated for the study.
Infant faecal *L reuteri* (cfu/ml)	■				■		Quantitative PCR	A molecular method to detect and measure the presence of particular marker genes of *L reuteri*, as a measure of compliance [77].

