### Aims and hypotheses

This double-blind, placebo-controlled randomised trial aims to determine whether the probiotic *L reuteri DSM 17938* benefits infants <3 months old (<13.0 weeks) with colic by reducing daily duration of infant crying/fussing. Secondary aims are whether there is reduced daily frequency of episodes of infant crying/fussing, and improved infant sleep, maternal mental health, and parent and family functioning. We also aim to investigate changes in gut microbiota, faecal calprotectin and *E coli* colonisation which are all possibly implicated in the mechanism of disease, and finally to determine whether probiotic use reduces healthcare costs in infant colic.

We hypothesise that, compared to the placebo (control) group, the *L reuteri* (intervention) group will have lower daily crying/fussing time per 24 hours at one month post randomisation. We further hypothesise that the *L reuteri* (intervention) group at 7, 14, 21, 28 days and 6 months post randomisation will have:

• lower crying/fussing time per 24 hours,

• fewer crying/fussing episodes per 24 hours,

• longer sleep duration,

• higher scores on a standardised measure of maternal mental health (one and six months),

• higher scores on a standardised measure of family functioning (one and six months), and

• higher scores on a standardised measure of parent quality adjusted life years (one and six months).

We also hypothesise that the intervention group compared to the control group will have (at one month):

• more diverse gut microbiota,

• lower faecal calprotectin levels, and

• less *E. coli* colonisation, thereby suggesting a potential pathophysiological mechanism in infant colic.

Finally, we hypothesise that the intervention will be potentially cost-saving to the health care system by diverting families away from more expensive management such as overnight stays at mother-infant units.

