#### Visit one

During the visit, the researcher reconfirms eligibility, asks the mother to complete the baseline questionnaire, and reviews with the family in detail the study diary, anticipated phone calls, the procedure of administering the study product to the infant, and the anticipated procedures at the end of the study. The researcher weighs the baby, collects the stool sample and transports it back to the RCH on ice in a portable cooler, and then stores it in the laboratory −80°C freezer.

#### Study period Days 1 – 28

On days 1, 7, 14 and 21 the study team sends a mobile text (SMS) message to families to remind families to fill in the weekly diary. Study researchers call families on day 28 to remind families to a) stop administration of the study product; b) fill in the one month questionnaire; c) collect a stool sample; and d) make an appointment for the second (final) visit.

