#### Compliance with the study product

Compliance is assessed by weighing of study bottles pre- and post- dispensing, collection of faecal samples at the end of the intervention period to assess for presence of *L reuteri* in each infant’s stool, and weekly diary to record administering of the product.

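### A between-arm difference in the day-28 stool diversity score would not by itself show a change in the resident microbiota, because the score as defined can include the administered L reuteri

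*Protocol article*

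**What the plan says.** - **The score.** Table 1 lists infant faecal microbiota diversity as a secondary outcome at day 0 and day 28, measured by 16S rDNA T-RFLP: "A molecular method to investigate the diversity within bacterial communities, given as a diversity score, with higher scores indicating more microbial diversity". The article does not name the index and sets no organism aside.
- **The exposure.** Under Treatment arms, dosage and route of administration: "Carers administer five drops of study product orally to each infant once daily for 28 days".
- **The timing of the stool.** Under Study period Days 1 – 28: "Study researchers call families on day 28 to remind families to a) stop administration of the study product". The same call asks them to "c) collect a stool sample". No interval between last dose and sample is planned.
- **The product in the stool.** Compliance with the study product includes "collection of faecal samples at the end of the intervention period to assess for presence of" L reuteri. Table 2 lists this as a quantitative PCR at day 0 and day 28: "A molecular method to detect and measure the presence of particular marker genes of" L reuteri.
- **The comparison.** Data analysis compares every secondary outcome between the two arms with t tests or non-parametric tests.
- **The reading.** Aims and hypotheses expects more diverse microbiota in the active arm. It names gut microbiota among factors possibly involved in the mechanism, and closes its list of three stool hypotheses with "thereby suggesting a potential pathophysiological mechanism in infant colic".

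**The concern.** The intervention is a bacterium and the outcome is a score over all bacteria in the stool. Exclusion criteria remove infants, and breastfeeding mothers, taking L reuteri at commencement. L reuteri from the product should therefore appear at day 28 mainly in the active arm, and adjusting for the baseline score would not remove it. Of the three mechanistic stool outcomes, only diversity has this feature; calprotectin and E coli load do not measure the product.

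What is at stake is interpretation. A score that moved only because the drops were taken could be reported as a shift in the infant's own flora. Conversely, a product-driven fall could hide a real gain in resident diversity.

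**Working it through.** **Plan's own figure.** The article gives no expected value, SD or power for the diversity score, so there is nothing to reproduce for this outcome. The trial's only sample size concerns crying time. For 0.5 SD, 80% power and two-sided 0.05 (sidedness assumed), the t-test needs 64 per arm, or 128 in total, and 128/0.8 = 160. That agrees with the article and is untouched by this point.

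**Inputs for the illustration (all assumed; the documents give none).** A resident community of k equally abundant fragments, k = 6, 10 or 15. One new, distinct fragment for L reuteri takes a share p of the signal, and the residents keep their relative proportions.

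**Shannon index.** Before: H = ln k. After: H = -[(1-p) ln((1-p)/k) + p ln p]. The change simplifies to

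ΔH = h(p) - p ln k, where h(p) = -(1-p) ln(1-p) - p ln p.

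Worked cases:
- k = 6, p = 0.10: h = 0.3251; 0.10 × ln 6 = 0.1792; ΔH = +0.146.
- k = 15, p = 0.02: h = 0.0980; 0.02 × ln 15 = 0.0542; ΔH = +0.044.
- k = 15, p = 0.50: h = 0.6931; 0.50 × ln 15 = 1.3540; ΔH = -0.661.

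| L reuteri share p | k = 6 | k = 10 | k = 15 |
|---|---|---|---|
| 0.1% | +0.006 | +0.006 | +0.005 |
| 2% | +0.062 | +0.052 | +0.044 |
| 5% | +0.109 | +0.083 | +0.063 |
| 10% | +0.146 | +0.095 | +0.054 |
| 50% | -0.203 | -0.458 | -0.661 |

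The largest possible rise is ln((k+1)/k), reached at p = 1/(k+1): 0.154 for k = 6 and 0.065 for k = 15. The index drops below its starting value once p exceeds about 37% (k = 6), 24% (k = 10) or 17% (k = 15).

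**Uneven communities.** With 5 to 20 taxa, even or geometrically declining (ratio 0.6), the pattern is the same. The rise is about 0.05 to 0.13 at 5%, and the index falls below its start above about 13% to 50%. The Simpson index also rises slightly at low share and falls at high share.

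**Richness.** A distinct new fragment adds one, a relative rise of 1/k: 17% for k = 6 and 7% for k = 15. If L reuteri shares a fragment length with a species already in the profile, richness does not change.

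**Reading.** With resident proportions held fixed, the product alone can move the score either way or hardly at all. Neither size nor direction can be derived from the article.

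**The case against.** The strongest reply has four parts.

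1. **The article does not say that L reuteri is counted.** One table cell describes the assay. Fragment handling belongs in a laboratory manual or SAP, and a journal article need not carry it. This stands: the silence is not a defect, and a reader should not infer that the score is known to include the product. What the article does fix is a community-wide score, an end-of-dosing sample and a mechanistic reading; the point rests on those three together.
2. **Detection by PCR does not prove a T-RFLP peak.** The compliance assay targets L reuteri marker genes, so a positive result does not show that the organism forms a visible, separate fragment in a community profile. This also stands. It rules out claiming that the product necessarily adds a fragment in the active arm, or that diversity is bound to rise there.
3. **The data to interpret the score are already planned.** L reuteri is quantified at the same two time points. A reader might infer that the mechanistic hypothesis is untestable or that a positive result would be a mere compliance readout; the documents do not support that. However, the PCR gives the amount of L reuteri, not the diversity of everything else, so it helps without settling the question.
4. **Total diversity is a legitimate outcome.** The Background describes bowel colonisation as part of how probiotics work and cites reduced Lactobacillus species in colic. Removing the fragment could also remove resident lactobacilli. This is a good reason not to replace the planned score, but it does not argue against a second version beside it.

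The mechanistic wording is also hedged, and its closing phrase is attached to the E coli item. The aims sentence nevertheless names gut microbiota explicitly, so the mechanistic reading does extend to diversity.

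**Conclusion.** The concern holds in a limited form. On the definition given, a between-arm difference in day-28 diversity could reflect the product's own signal, a change in the resident flora, or both, and the score alone cannot separate them. Under the assumed even communities of 6 to 15 fragments, the product alone shifts Shannon by about +0.005 at 0.1% of signal, +0.04 to +0.15 at 2% to 10%, and -0.20 to -0.66 at 50%. These figures assume a distinct fragment and unchanged resident proportions. No between-infant SD is given, so they cannot be put on a standardised scale.

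The documents do not support the stronger reading that diversity will be inflated in the active arm: the bias has no fixed direction and may be negligible. The point affects the interpretation of one secondary outcome. It is a worthwhile refinement, not a flaw in the trial's main inference.

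**What to change.** Keep the planned diversity score as the secondary outcome and prespecify, before unblinding:

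- a sensitivity analysis that removes the terminal fragment(s) matching L reuteri and rescales the remaining profile to its total, applied identically in both arms and at day 0 and day 28;
- reporting of both versions alongside the planned L reuteri PCR;
- a rule that a change in resident diversity is put forward as a possible mechanism only if the difference persists without the L reuteri fragment.

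If the full protocol, laboratory manual or SAP already does this, a cross-reference is enough.

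The cost is one further calculation on profiles already generated, with no new samples or visits. The drawback is that resident species sharing the fragment, possibly other lactobacilli, are removed with it. That is why this should be a sensitivity analysis and not a replacement.

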### Study procedure details

Figure 1 and Figure 2 show details of study procedures.

**Figure 1 F1:**
[figure not shown]
Study procedures.

**Figure 2 F2:**
[figure not shown]
Perera diagram showing treatment and follow-up procedures.

#### Recruitment

Eligible families who present through the RCH ED are identified in three ways: i) by the treating doctor, ii) by the ED social worker, or iii) through the ED electronic database. Eligible families who present through the RCH Unsettled Babies Clinic are identified by their treating doctors. Eligible families who present through the Boroondara and Moonee Valley Maternal and Child Health Nurses and Tweddle Child and Family Services are identified by their nurses or intake worker. Potentially eligible families are referred to study team members, who call families or approach them in the ED or clinic if appropriate.

The study team establishes eligibility criteria. Infants and breastfeeding mothers who are on a paediatrician-recommended dairy-free diet, infants who are taking *L reuteri*/solids/antibiotics, and breastfeeding mothers who are taking *L reuteri* at the time of study enrolment are reassessed for eligibility by telephone call after two weeks. Eligible families are approached for consent. Each family can choose to be visited at home or attend a visit at RCH for the first study visit. Study researchers call the families one day before the proposed study visit to confirm the home or RCH visit. During this call, study researchers reconfirm eligibility and consent, remind families who have not completed the consent form and baseline questionnaire to complete them, and instruct caregivers to collect a stool sample from their babies and store it in a freezer. Study researchers also record on the Clinical Record Form whether the babies are breast- or bottle-fed.

#### Visit one

During the visit, the researcher reconfirms eligibility, asks the mother to complete the baseline questionnaire, and reviews with the family in detail the study diary, anticipated phone calls, the procedure of administering the study product to the infant, and the anticipated procedures at the end of the study. The researcher weighs the baby, collects the stool sample and transports it back to the RCH on ice in a portable cooler, and then stores it in the laboratory −80°C freezer.

#### Study period Days 1 – 28

On days 1, 7, 14 and 21 the study team sends a mobile text (SMS) message to families to remind families to fill in the weekly diary. Study researchers call families on day 28 to remind families to a) stop administration of the study product; b) fill in the one month questionnaire; c) collect a stool sample; and d) make an appointment for the second (final) visit.

#### Visit two

During the second visit, the researcher weighs the infant, and collects a) the study diary; b) the one month questionnaire; c) the study product bottle and d) a stool sample which is transported back to the RCH on ice in a portable cooler, and then stored in the laboratory -80°C freezer.

#### Six month follow-up

At six months, the families are sent a letter together with a 24-hour study diary, a questionnaire and a reply-paid envelope. Caregivers are asked to complete the study diary and questionnaire, and return both in the enclosed reply-paid envelope.

#### Compliance with the study product

Compliance is assessed by weighing of study bottles pre- and post- dispensing, collection of faecal samples at the end of the intervention period to assess for presence of *L reuteri* in each infant’s stool, and weekly diary to record administering of the product.

### Data analysis

#### Estimation of sample size

We have selected a sample size of 160 to provide 80% power to detect a minimum effect size of 0.5 standard deviations, difference in the mean daily crying time between treatment groups with a significance level of p < 0.05, allowing for a drop out rate of 20%. If the data are substantially skewed, 80% power would be maintained to detect a minimum effect size of 0.525 [63,64]. In Savino’s trial [60], the percentage reduction in median daily crying time at day 28 compared to baseline was 70% for the probiotic and 26% for simethicone, suggesting substantive differences in this outcome are likely. With a much larger sample size (double that of Savino’s trial) in our study, we are confident we would also be able to detect a smaller difference in daily crying time reduction. Our sample size of 160 infants provides 80% power to detect a minimum effect size of 0.85 standard deviations, difference in the mean daily crying time between treatment groups within either the formula-fed or breastfed babies, assuming 40% of infants in the sample are exclusively breastfed.

We will be conducting an intention-to-treat analysis in which participants are compared according to the group to which they were randomly allocated regardless of participants' compliance, crossover to other treatments or withdrawal from the study. This approach preserves the prognostic balance in the study arms achieved by randomisation.

Baseline characteristics and study outcomes will be described for each treatment group using means and standard deviations for normally distributed continuous outcomes, while medians and inter-quartile ranges will be used for continuous outcomes that are skewed. Proportions for categorical data will be given. All primary and secondary outcomes for the intervention versus control groups will be compared with t tests and non-parametric tests for continuous data, and chi squared tests for dichotomous data. The primary outcome is the crying time/24 hours at day 28. We will additionally consider a dichotomised indicator of treatment response defined as a 50% reduction in crying time. Subgroup analyses are intended a priori to examine treatment differences amongst breastfed babies and those who are formula-fed, and amongst infants with a family history of atopy and those without.

Regression models will be used to estimate treatment effect sizes, odds ratios and 95% confidence interval, adjusting for potential confounding factors identified a priori and measured at baseline. These include infant age (≤6 weeks versus >6 weeks, taking into account the natural course of infant colic symptomatology with the peak of crying at six weeks), mode of birth delivery, maternal smoking, use of antibiotics or probiotics in infants and breastfeeding mothers, maternal diet if breastfeeding, maternal mental health scores, and known causes of crying (e.g. fever, eczema, vaccination, vomiting, and diarrhoea). Random effects regression models will be used for further longitudinal analysis examining trends in crying time within individual babies.

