### Randomisation

A block randomisation schedule to maintain balance between treatment arms has been prepared by an independent statistician, not directly involved in the analysis of the study results, from the Clinical Epidemiology and Biostatistics Unit (CEBU) at the RCH and supplied to Pharmacy who dispense the study product. Randomisation is stratified by method of infant feeding (breastfed versus formula-fed) and age at the time of study commencement (≤6 weeks versus >6 weeks, due to the natural crying peak occurring at around six weeks of age). Infants on a mixture of both breast- and formula-feeding are allocated to the formula-fed stratum. To minimise potential biases, the study is double-blind whereby treatment allocation is concealed from all study investigators and participants.

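### The primary day-28 test does not by itself keep the randomised balance that the plan claims despite withdrawal, and the model that could use the earlier diaries is kept for secondary trends

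*Protocol article*

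**What the plan says.** All references are to the protocol article.

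- **Primary comparison** (Data analysis, under Estimation of sample size). The primary outcome is crying time per 24 hours at day 28. Primary and secondary continuous outcomes are compared between arms by t tests and non-parametric tests.
- **Sample size** (same section). "We have selected a sample size of 160 to provide 80% power to detect a minimum effect size of 0.5 standard deviations", "with a significance level of p < 0.05", "allowing for a drop out rate of 20" per cent.
- **Intention-to-treat** (same section). Participants are compared by allocated group whatever their compliance, "crossover to other treatments or withdrawal from the study". The next sentence says that this keeps the arms prognostically balanced as randomised.
- **Other models** (end of Data analysis). Regression adjusts for factors measured at baseline. Then: "Random effects regression models will be used for further longitudinal analysis examining trends in crying time within individual babies". No time points are given for that model.
- **Diaries** (Table 1; Study period Days 1 – 28; Visit two). Crying/fussing time is scheduled at days 0, 7, 14, 21 and 28 and at six months. During treatment, families receive text reminders to fill in the diary. The researcher collects it at visit two, and no earlier return is described.

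**The concern.** A two-group test at one time point can include an infant only if there is a value at that time, observed or imputed. The plan expects about a fifth of infants to be lost, yet says its approach holds regardless of withdrawal and keeps the randomised balance. Randomisation balances the 160 infants allocated. It does not balance a subset defined by who stayed.

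If families leave because of how much the baby cries, and this differs between arms, the infants left at day 28 are no longer comparable and the primary estimate is biased. The plan schedules three diaries between baseline and day 28 and names a type of model that can use them, but gives that model no part in the primary estimate.

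**Working it through.** **1. The plan's own sample size.** Inputs from Estimation of sample size: 0.5 SD, 80% power, significance level 0.05, 20% drop-out. Two-sided testing and 1:1 allocation are my assumptions; the Randomisation section mentions only "A block randomisation schedule to maintain balance between treatment arms".

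- Normal approximation: n per arm = 2(z₀.₉₇₅ + z₀.₈₀)² / d² = 2(1.960 + 0.842)² / 0.5² = 62.8, so 63. Total 126, and 126 / 0.8 = 157.5, so 158.
- Exact t test: 63.8, so 64 per arm. Total 128, and 128 / 0.8 = 160, the stated figure.
- Exact power at 0.5 SD: 80.1% with 64 per arm, 88.2% with 80 per arm.

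The stated 80% is therefore the power of about 128 infants with a day-28 value, with 160 − 128 = 32 lacking one. The size is correct, and it fits a primary test planned on available data.

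**2. What the named analyses can use.**

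| Analysis | Role in the article | Infant with early diaries but no day-28 value |
|---|---|---|
| t or rank test, day 28 | primary | contributes nothing unless imputed |
| Regression on baseline factors | adjusted effect sizes | same for the day-28 outcome; baseline factors carry nothing from days 7 to 21 |
| Random effects model | further trend analysis | can contribute, if the diary is recovered |

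**3. Size of the possible bias.** The documents give no correlation between diaries and no drop-out mechanism, so every input here is illustrative. Setting: no true effect, 20% drop-out per arm, drop-out logistic in the day-21 value (slope 1 per SD where present), correlation ρ between days 21 and 28 of 0.4, 0.6 or 0.8, and 400,000 infants per arm. The table gives the absolute bias in SD.

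| Drop-out depends on crying | ρ = 0.4 | ρ = 0.6 | ρ = 0.8 | Using the day-21 value |
|---|---|---|---|---|
| same way in both arms | 0.00 | 0.00 | 0.00 | about 0 |
| in one arm only | 0.07 | 0.10 | 0.14 | about 0 |

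The one-arm figures scale with ρ as they should: 0.104 / 0.6 = 0.17 and 0.139 / 0.8 = 0.17, the shift in the mean day-21 value among those who stay.

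A second simulation used a true effect of −0.50 SD and about 20% drop-out after day 14, depending on the day-14 value. Infants with day-28 data gave −0.483 when the mechanism was the same in both arms, against −0.498 from an analysis valid under missing at random (1 − 0.483/0.498 = 3%). When drop-out depended on crying in the placebo arm only, they gave −0.397 against −0.502, a difference of 0.105 SD, which lies inside the 0.07 to 0.14 range.

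**4. Scale.** Against the design effect, 0.07 / 0.5 = 14% and 0.14 / 0.5 = 28%. The standard error of the difference with 64 per arm is √(2/64) = 0.177 SD, so the bias would be 0.4 to 0.8 of a standard error. Loss of heavy criers from placebo only would shrink the estimate; loss from the probiotic arm only would inflate it.

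**The case against.** **No contradiction in terms.** The intention-to-treat sentence says in which arm an infant is analysed, and a day-28 test by allocated arm obeys it. This stands. A reader might infer that the plan breaks its own intention-to-treat promise, but the wording does not go that far. What is too broad is the sentence after it, which claims the balance without limiting it to analysis by allocated group.

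**Restriction to completers is not stated.** A reader might infer that the article limits the primary test to infants with a day-28 diary. It does not say so. It is silent on missing values, and the full protocol or SAP may impute. That silence is no finding. The point rests on what the article does fix: the test, the expected loss, the balance claim and the lesser role of the longitudinal model.

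**The early diaries may not be in hand.** This also stands, and it limits the remedy. With collection at visit two and no interim return described, a family that leaves early may hand back nothing. It cannot be assumed that drop-outs' diaries already exist in the trial data or that the change needs no retrieval.

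**The bias may be negligible.** A double-blind trial with an identical placebo makes drop-out that differs by arm less likely, though not impossible. Families who merely stop the drops remain in the comparison if they return a day-28 diary. A reader might fear that nearly half the effect could be lost. In the second simulation the estimate does fall to −0.270, a 46% attenuation, but only if drop-out depends on crying in opposite directions in the two arms. Nothing in the documents suggests this, and the ordinary reasoning that families of babies who keep crying leave points the same way in both.

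**A single-time-point test is legitimate, and crying time may be skewed.** Both are true. A mixed model therefore needs its own provision for skewness.

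**Conclusion.** The point holds in limited form. The article fixes a day-28 two-group test as primary and sizes it on about 128 of 160 infants. It then claims a preserved balance that this test, without imputation, does not secure. The model that could use the earlier diaries is left to further analysis.

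The likely cost is uncertain. Bias is near zero if drop-out works the same way in both arms, and about 0.07 to 0.14 SD if it depends on crying in one arm only. These figures rest on assumed correlations of 0.4 to 0.8, 20% loss per arm and an assumed drop-out slope. The advantage of using earlier diaries rests further on data being missing at random given those diaries, and on the diaries being recovered. The sample size itself needs no change. The point is worth acting on because the remedy is cheap, not because the planned test is invalid.

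**What to change.** - **Primary estimate.** Take the day-28 treatment difference from a mixed model on the day 7, 14, 21 and 28 diaries, with visit as a category, treatment-by-visit, baseline crying/fussing time and the randomisation strata (feeding method and age group). Include every randomised infant with any post-baseline diary. State in advance a transformation, or a robust or rank-based check, in case the data are skewed.
- **Sensitivity analyses.** Keep the day-28 available-case t or rank test. Add a delta-shift analysis that makes the outcomes of infants who withdrew progressively worse, by arm.
- **Wording.** Limit the balance sentence to analysis by allocated group, and say that missing day-28 values are dealt with separately.
- **Data.** Ask families who withdraw to return the diary pages already completed. The model's gain over the day-28 test depends on this.

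Cost: a change of wording, slightly more analysis work, reliance on a missing-at-random assumption that the delta shift then probes, and the effort of retrieving partial diaries. The same model also gives the day 7, 14 and 21 crying-time contrasts that are already secondary outcomes.
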